## 2. Changes from Protocol including Amendments

One interim analysis after 30 evaluable patients is planned in the study protocol. As it is expected that – due to expiration of available study medication – in total only a few more evaluable patients will be enrolled than planned for the interim analysis, the interim analysis is skipped. There will only be one final analysis of study data.

The study protocol defines only the Full analysis set for analysis of efficacy but requires in addition evaluability of patients in the sample size estimation. To address this, the Per protocol set is introduced in this SAP as secondary analysis population.

The study protocol states that qualitative parameters spread in very large contingency tables will be analyzed with the asymptotic chi-square-test, but as such data do not occur this test is not used in this SAP.

According to the study protocol, demographic and pre-treatment characteristics that are continuous should be analyzed by a general linear model (GLM) to determine comparability of the ancrod and placebo groups at baseline. If treatment group differences were seen at the 0.10 level of significance, these variables would be added as stratification variables or covariates to the efficacy analyses. As the study is randomized, it was decided to not follow this request and to not assess baseline differences.

The study protocol leaves open whether an analysis of covariance or a general linear model should be used to evaluate the primary efficacy variable and quantitative secondary efficacy variables. As the primary efficacy variable (change from Baseline) may be dependent on the baseline value, the baseline value should be taken into account for the primary analysis as covariate. For this reason, statistical evaluation will be performed using a generalized linear model, without prior investigation at the BDRM.

Introduced by several protocol amendments, various changes have been implemented in the CRF. However, the statistical analysis of patients being included in the study prior to an implemented CRF change is not affected, and values will be missing for added CRF parameters for all patients enrolled under a previous protocol amendment; a footnote for the respective summary tables will clarify the data issues referring to CRF amendments. In detail, the following changes relevant for the statistical analysis were made to the CRF:

- Exclusion criterion 17 was added with Amendment 4.1
- Exclusion criterion 37 was added for Czech centers only with Amendment 4.2 and for German centers with Amendment 5.0
- Exclusion criterion 14 was rephrased with Amendment 4.1
- Exclusion criteria 5 and 11 and 14 were rephrased with Amendment 5.0
- For the module "Speech intelligibility test" (Screening visit, Visit 5, Visit 6, Visit 7), an additional question was added with Amendment 4.1 ("Loudness with which 50 % of single words are understood (affected ear)")
- For the module "Vertigo" (Screening visit, Visit 5), an additional nystagmography method was added with Amendment 4.1 ("Frencl's goggles" synonymously for Frenzel goggles)
- Laboratory values were initially separated in local laboratory and central laboratory (Screening visit, Visit 5); with Amendment 4.1 they were displayed together and various lab parameters from the central laboratory were added to the CRF
- With Amendment 4.1, comment sections were added to the CRF at the end of a visit's documentation.

The database indicates what CRF version is used for a given patient.

### 3. Study Overview

#### 3.1. Study Objectives

The primary objective of this study is to evaluate the efficacy of ancrod as primary treatment of SSHL compared to placebo in patients with unilateral idiopathic SSHL as determined by pure tone audiometry (PTA).

The secondary objectives of this study are to evaluate the relationship between biomarkers and clinical efficacy and to investigate the safety and tolerability of ancrod.

#### 3.2. Study Design

This study is performed as a randomized, double-blind, multi-center, placebo-controlled, parallel-group phase II proof-of-concept study.

Study treatment and all study assessments are performed in an outpatient setting at study sites.

After obtaining informed consent, patients presenting with unilateral SSHL within 7 days after onset are screened for eligibility. Patients meeting all in- and exclusion criteria (including the screening audiometric assessments) are randomized into 2 cohorts in a ratio of 2:1 between active treatment (ancrod) and placebo. All screening assessments including randomization and patient enrollment are to be performed within 36 hours.

Immediately after randomization on Day 1 (Visit 1), patients receive the initial intravenous infusion of investigational product. The initial dose of study drug is adjusted according to the screening fibrinogen concentration by using different infusion durations at a constant infusion rate.

On the following day (Day 2, Visit 2), a venous blood sample is taken for coagulation assays. Thereafter, a weight-adjusted ancrod dose of 1 IU/kg (or placebo when randomized to placebo) is administered subcutaneously. The result of the coagulation assay is not communicated from the laboratory to the investigator or any other blinded study personnel; it is received by a dedicated unblinded person only. If the fibrinogen concentration on Day 2 is lower than 50 mg/dL, the unblinded person informs the investigator that the respective patient may not receive further injections of study drug on Day 4 and Day 6. If the fibrinogen concentration on Day 2 is  $\geq 50$  mg/dL, the investigator is informed by the unblinded person that the patient may receive further subcutaneous injections of 1 IU/kg ancrod (or placebo when randomized to placebo) on Day 4 and Day 6 (Visits 3 and 4).

On Day 8 (Visit 5) the treatment effect is evaluated by means of audiometry and speech recognition, and the presence and intensity of tinnitus and vertigo is determined. If no improvement of clinical signs and symptoms compared to the baseline value is achieved, the patient is allowed to switch to corticosteroid treatment, vasodilators, vitamin C, vitamin B12 or antihistamines if deemed necessary at the discretion of the investigator.

During the follow-up visits on Day 30 and Day 90 (Visits 6 and 7), the treatment effect is again determined by audiometric evaluation and tinnitus intensity to monitor for signs of relapse in the affected ear.

A schedule of assessments is given in Appendix 13.1. The study flowchart illustrates the study design:

[figure not shown]

### 3.2.1. Target Population

Desired study patients for enrolment are patients with unilateral SSHL as determined by audiometry.

### 3.2.2. Blinding

The study is carried out in a double-blind, placebo-controlled study design; neither the patient nor the investigator nor any staff collecting, reviewing or cleaning study data have knowledge of the treatment a patient receives. This applies also to any staff analyzing study data at YYY until final unblinding.

To ensure the blinding throughout the study, the following measures are taken:

- Both treatments are indistinguishable in appearance
- Appearance and labeling of vials and treatment kits do not provide any information which disclose the treatment group
- The vials and treatment kits are identified via a kit number only.

In case of medical emergency, or when information about a patient's treatment group is required in order to determine the further treatment of the patient, unblinding of individual patient's treatment can be achieved by opening the respective numbered emergency envelope. Unblinding of patients is also performed for notification of a SUSAR. Investigators have to document immediately every premature unblinding of a patient (e.g. accidental unblinding) in the CRF.

Regular unblinding for all patients including transfer of data on coagulation, biomarkers and anti-ancrod antibodies will only be done for the purpose of the final statistical analysis, after determination of the analysis populations in the BDRM and closure of the database.

### 3.2.3. Randomization

Treatment assignment is pre-planned according to a computer generated randomization schedule in a 2:1 (verum : placebo) ratio. Randomization is not stratified by a baseline parameter, but provides a stratification by center using the block randomization method to achieve approximately a 2:1 allocation within each center and includes the site number and patient number within site with the assigned treatment. The randomization list was generated using commercial software (RANCODE Professional, Version 3.6) by an unblinded statistician at XXX. The unblinded statistician is excluded from any other study operation. The randomization list is kept by XXX and will be provided to YYY upon request after database closure.

Each center was instructed to use the investigational products provided in ascending order, taking care of the chronological order of the patients' inclusion starting with the investigational product with the lowest number available at the site. The first study drug administration is documented in the CRF stating the precise date and time.

In the statistical analysis, treatment groups will be denoted as "Ancrod" or "Placebo", respectively.

## 3.3. Study Conduct

Duration of trial:

- Per patient: Screening period of up to 36 hours, then 1-week double-blind treatment phase, then 12-week follow-up phase without study treatment
- First patient in (FPI): August 2013
- Last patient out (LPO): planned for September 2018.

The study is conducted in 24 sites in Germany and Czech Republic; whereas 8 sites enrolled actively patients.

### 3.4. Study Variables

#### 3.4.1. Primary Efficacy Variable

The primary outcome measure of the study is:

- Change in PTA (Air) in the affected ear from Screening (Day 1; Visit 1) until Day 8 (Visit 5). The PTA will be calculated as the arithmetic mean of air conduction thresholds at the affected consecutive frequencies in the frequency range of 0.125 to 8 kHz. A non-affected frequency within two affected frequencies will be included.

#### 3.4.2. Secondary Efficacy Variables

Secondary outcome measures include (according to the protocol):

- Change in word recognition score from Screening to Day 8, Day 30 and Day 90
- Change in PTA (Bone) in the affected ear from Screening to Day 8, Day 30 and Day 90
- Change in PTA (Air) in the affected ear from Screening to Day 30 and Day 90
- Change in fibrinogen concentration from Screening to Day 2 and Day 8
- Change in biomarkers from Screening to Day 8
- Patient assessment of change in hearing impairment
- Physician assessment of change in hearing impairment
- Change in tinnitus severity
- Nystagmography change from Screening to Day 8.

The exact definition of the respective secondary efficacy variables is given in Section 9.2.

#### 3.4.3. Safety Variables

Clinical safety assessments include:

- Adverse event reporting
- Change from Screening to Day 8 in general physical examination findings
- Change from Screening to Day 8 in otolaryngological examination findings
- Change from Screening to Day 8 in vital signs
- Change in laboratory parameters
- Occurrence of neutralizing anti-ancrod antibodies at Screening, Day 8, and Day 30.

### 3.5. Sample Size Determination

Sample size determination for this study is based on 2-sided t-tests with a global alpha level of 5 % and a statistical power of 90 %. A standard deviation of 20 dB for the test statistic is assumed. In order to be able to confirm a treatment difference of 15 dB PTA of active treatment versus placebo with a 2:1 randomization, a total number of 87 evaluable patients will be required, 58 patients in the group receiving ancrod, and 29 patients receiving placebo. To compensate for dropouts, a total number of 99 patients is planned to be enrolled, 66 patients receiving ancrod, and 33 patients receiving placebo.

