## **10**      **Statistics**

### **10.1**      **Sample Size Determination**

Sample size determination for this study is based on 2-sided t-tests with a global alpha level of 5% and a statistical power of 90%. A standard deviation of 20 dB for the test statistic is assumed. In order to be able to confirm a treatment difference of 15 dB PTA of active treatment versus placebo with a 2:1 randomization, a total number of 87 evaluable patients will be required, 58 patients in the group receiving ancrod, and 29 patients receiving placebo. To compensate for dropouts, a total number of 99 patients is planned to be enrolled, 66 patients receiving ancrod, and 33 patients receiving placebo.

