### 5. Statistical/Analytical Issues

#### 5.1. General Considerations

Based on the raw database containing the recorded CRF data and on other data such as protocol deviations and central lab data, analysis data sets according to internal standards will be programmed that will be used for the generation of summary tables, figures and listings (TFLs). To meet common quality control requirements, the analysis of the following variables will be double-programmed by a second biostatistician:

- Change in PTA (Air) in the affected ear from Visit 1 to Visit 5 (including the corresponding analysis data set needed for the primary efficacy variable)
- Adverse event rates.

For all other TFLs, a second biostatistician will review the SAS program codes and will check the results for consistency at least visually. All SAS programs used for the evaluation will be stored in a study-specific directory on the YYY file server together with the corresponding 'list' and 'log' files.

Quantitative efficacy variables (including the primary efficacy variable) will be analyzed by means of an analysis of covariance (ANCOVA) based on the generalized linear model (SAS procedure PROC GLM). Underlying model assumptions, such as normality and homogeneity of variance, will be assessed at the BDRM. Should these assumptions be violated, appropriate data transformations or the choice of a non-parametric analysis method will be considered. These analyses will be performed for the primary efficacy variable in addition to the originally planned analysis.

For the primary efficacy variable, confirmative testing will be performed with the aim to show superiority in favor of the treatment with ancred over placebo. Basically, a two-sided 5 % significance level will apply. All other variables will be exploratively compared between treatment groups.

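### SAP 3.5 still gives 90% power with 87 evaluable patients as the current design, although SAP 2 expects only slightly more than 30, where power for 15 dB is about 46% to 58%

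*Combined protocol and SAP*

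**What the plan says.** The sample size statement is the same in Protocol 10.1 and SAP 3.5. The protocol says that "a total number of 87 evaluable patients will be required", split 58 to ancrod and 29 to placebo, with 99 to be enrolled (66 and 33). The SAP gives the inputs: two-sided t-tests "with a global alpha level of 5 % and a statistical power of 90" percent, "A standard deviation of 20 dB for the test statistic is assumed", and the aim to "confirm a treatment difference of 15 dB PTA of active treatment versus placebo with a 2:1 randomization". SAP 5.3 adds that a 12% dropout rate was allowed for.

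SAP 2 lists departures from the protocol. It cancels the interim analysis, planned at 30 evaluable patients, because the study medication is expiring and it is expected that "in total only a few more evaluable patients will be enrolled than planned for the interim analysis". There will be one final analysis. SAP 2 draws no consequence for power or precision.

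SAP 5.1 states that for the primary variable "confirmative testing will be performed with the aim to show superiority", at a two-sided 5% level. SAP 9 and 13.5 say the same. SAP 5.6 says that no power adjustments are needed, but this concerns multiplicity, not the shortfall in patients. The available text contains no power, detectable difference or interval width for the size now expected.

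**The concern.** SAP 2 and SAP 3.5 cannot both describe the trial that will be analysed. SAP 3.5 is written in the present and future tense and is not marked as history, so 90% power, 87 evaluable and 99 enrolled read as properties of the current study.

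What is at stake is how the result is read. If the primary test is not significant, the only power figure in the plan invites the conclusion that a 15 dB effect has been tested with 90% power and not found. At a little over 30 patients, a true 15 dB effect would be missed about half the time under the SAP's own assumptions. Conversely, the observed difference would have to be about as large as the planned effect to reach significance, so a significant estimate would tend to overstate the true effect.

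**Working it through.** **Inputs.** From SAP 3.5: difference δ = 15 dB, SD σ = 20 dB, two-sided α = 5%, power 90%, 58 + 29 = 87 evaluable, 99 enrolled. From SAP 3.2.3: 2:1 allocation. From SAP 5.3: 12% dropout. From SAP 2: interim size 30, final size a few more than that. The range of 30 to 40 evaluable patients is my assumption, since no number is given.

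**1. Reproduce the plan's figures.** Placebo group size by the normal formula:

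n = (1 + 1/2) × (1.960 + 1.282)² × (20/15)² = 1.5 × 10.51 × 1.778 = 28.02, rounded up to 29.

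This gives 58 + 29 = 87. Exact (noncentral t) power at 58:29 is 90.3%. Enrolment: 87 / (1 − 0.12) = 98.9, rounded up to 99. The stated figures reproduce.

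**2. Same inputs at the expected size.** SE = 20 × √(1/n₁ + 1/n₂); noncentrality λ = 15/SE; df = n₁ + n₂ − 2; power = P(|T(df, λ)| > t(0.975, df)); 95% CI half-width = t(0.975, df) × SE.

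| Ancrod:placebo | SE (dB) | λ | t(0.975, df) | Power for 15 dB | Half-width (dB) | Difference detectable at 90% power (dB) |
|---|---|---|---|---|---|---|
| 58:29 (design) | 4.55 | 3.30 | 1.988 | 90.3% | 9.0 | about 15 |
| 20:10 | 7.75 | 1.94 | 2.048 | 46.4% | 15.9 | 26.0 |
| 22:11 | 7.39 | 2.03 | 2.040 | 50.3% | 15.1 | 24.7 |
| 24:12 | 7.07 | 2.12 | 2.032 | 54.0% | 14.4 | 23.6 |
| 27:13 | 6.75 | 2.22 | 2.024 | 58.1% | 13.7 | 22.5 |

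The normal approximation is 2 to 3 points higher in the last four rows (49.1%, 52.8%, 56.4%, 60.3%). The half-width is also the smallest observed difference that reaches p < 0.05. The conclusion does not depend on a narrow reading of a few more: even 60 evaluable patients (40:20), twice the interim size, give 76.8%.

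**3. Baseline adjustment.** The primary model includes baseline PTA (SAP 5.2). If baseline has correlation r with the outcome, the residual SD is 20 × √(1 − r²). The documents give no r. Assuming r = 0.5, the SD is 20 × √0.75 = 17.3 dB, and with one degree of freedom spent on the covariate the power is 57.8%, 62.2%, 66.2% and 70.5% at N = 30, 33, 36 and 40. At r = 0.3 it runs from 49.9% to 62.1%, and at r = 0.7 from 74.4% to 85.8%. None reaches 90%.

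**4. Centers.** Spending 8 further degrees of freedom on centers lowers the unadjusted power by about one point (46.4% to 45.4% at N = 30; 58.1% to 57.6% at N = 40).

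**The case against.** The strongest reply is that SAP 3.5 records how the trial was sized, that the calculation is right, and that SAP 2 openly discloses the shortfall before the reader reaches 3.5. All three parts are fair. A reader might infer that the sample size was miscalculated; it was not, and Protocol 10.1 is not at fault either. But the disclosure stops at cancelling the interim analysis. SAP 3.5 is not labelled as history and does not refer back, so the contradiction remains.

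A reader might also infer that enrolment is known to stop at a fixed number, or that power is exactly one half. SAP 2 states an expectation without a final N, and the planned analysis is an ANCOVA rather than a t-test, so only a labelled range is defensible. The primary set is the FAS with baseline carried forward for a missing Visit 5 value (SAP 4.1, 5.3). It may be somewhat larger than the evaluable set, but carried-forward values count as zero change and would not restore 90%.

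The most tempting stronger reading is that the confirmatory label is now invalid. The documents do not support that. One pre-specified primary variable tested at two-sided 5% keeps its type I error at any sample size. Nor can it be said that the plan lacks a confidence interval for the primary effect: part of the primary-analysis text is not available, and SAP 13.4 sets a display format for two-sided intervals. Resting the conclusion on the interval instead of the p-value would in any case change presentation, not inference.

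**Conclusion.** The point holds as an unreconciled statement, not as an arithmetic error. The 90% belongs to a trial that SAP 2 no longer expects. For the trial it does expect, the same inputs give roughly half that power, and an interval more than one and a half times as wide as designed (13.7/9.0 = 1.5 at N = 40; 15.9/9.0 = 1.8 at N = 30). The size rests on two assumptions that the documents do not settle: a final evaluable count of 30 to 40, and how much baseline PTA explains. Varying both over plausible values moves the power but does not bring it to 90%. Type I error is unaffected; the harm lies in how a non-significant result, or the size of a significant one, would be read.

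**What to change.** In SAP 3.5:

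- Label the 87/99 calculation as the original design and cross-refer to SAP 2.
- Add power and 95% CI half-width (or the detectable difference) at the expected final size, as a range with assumptions labelled. With the SAP's inputs and an assumed 30 to 40 evaluable patients: about 46% to 58% power for 15 dB, half-width about 14 to 16 dB, and 22.5 to 26.0 dB detectable with 90% power. If baseline adjustment is credited, state the assumed correlation.
- Add one sentence that non-significance at this size will not by itself be read as evidence against a 15 dB effect.

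The test, its alpha and its confirmatory status need not change, and no more patients are needed. SAP 1 provides for signing before the blind data review, so the text can be changed without knowledge of treatment. The cost is a few lines and a less favourable stated power.

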## 4. Data Analysis Considerations

### 4.1. Analysis Populations

All patients having signed informed consent and provide any data in the CRF, whether receiving study treatment or not, will be considered for analysis ("*Enrolled patients*"). All patients who have been given a patient number for randomization at Visit 1 are included in the *Randomized set* independently of having received IMP. The following analysis populations that will be used for statistical evaluation will be defined:

- **Safety Set (SFS):** It includes all patients who take at least one IMP dose and for whom any safety-related data or information after the first dose of IMP are available.  
Patients will be analyzed as treated. Analysis of safety variables will be based on the SFS.
- **Full Analysis Set (FAS):** It includes all patients being randomized and receiving at least one IMP dose, regardless of any protocol deviations.  
The intention-to-treat principle is preserved despite the exclusion of patients who took no IMP, as the decision of whether or not to begin treatment could not be influenced by knowledge of the assigned treatment.  
Patients will be analyzed as randomized. The FAS is the primary population and will be used to analyze all baseline/background and efficacy variables.
- **Per Protocol Set (PPS):** It includes only patients who receive at least one IMP dose and fulfil the following evaluability criteria: have SSHL as defined per inclusion criterion 1, provide valid PTA data for Visit 1 and Visit 5, and adhere reasonably well to the study protocol without major protocol deviations (see Section 4.5).  
The PPS is a subset of the FAS and represents the secondary analysis set for baseline/background and efficacy variables.

A definite allocation of patients to analysis sets is made at the BDRM (see Section 4.5).

